# STUDY DESIGN

## Overall design

A feasibility study will be undertaken for this three-component intervention project. A feasibility study is in keeping with the MRC and NIHR framework which states that for complex interventions, a feasibility study is done to assess and refine the intervention prior to carrying out a full-scale evaluation (63). In terms of study design, a quasi-experimental one group time series design will be used.

## Stopping rules or discontinuation criteria

We will collect data on patients once they are admitted to the unit. Once they are discharged (including back to acute care, another site or back home) we will discontinue collecting data on the patient and we will keep track of their discharge disposition. If the patient after consenting decides to discontinue being in the study, we will withdraw them from the study.

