# OUTCOME MEASURES

**Data Collection**

Demographic variables, including age, sex, gender, race/ethnicity, education, socioeconomic status, highest level of education, and number of co-morbidities will be collected before the start of the intervention (Appendix E). Data on hospital admission diagnosis and length of hospital stay prior to TCP admission will also be collected (Appendix E). Demographic data and outcome data at T1 will be obtained within the first month of the patient’s admission to the TCU.

Table 2 outlines the outcome measurement tools that will be used to assess the participants, time points at which they will be measured, and the type of statistical test that will be used to analyze the results. The total expected time for tests is 37 minutes at T1, and 29 minutes at T2 and 45 minutes at T3.

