**Table 2. Outcome Measurement Tools, Time Points, and Statistical Tests**

| **Research Question**  **Number** | **Outcome (Tool)** | **Time Points** | | | | | | | | **Type of Statistical Test** |
| --- | --- | --- | --- | --- | --- | --- | --- | --- | --- | --- |
|  |  | **Pretest**  **Initial Assessment**  **(T1)** | **Weeks of Intervention** | | | | | | **Posttest (Immediately after 6-week intervention) (T3)** |  |
|  |  |  | **1** | **2** | **3** | **4**  **(T2)** | **5** | **6** |  |  |
| 1 | Recruitment Rate  (documentation) | √ |  |  |  |  |  |  |  | Descriptive statistics |
|  | Retention Rate  (documentation) | √ | √ | √ | √ | √ | √ | √ | √ | Descriptive statistics |
|  | Adherence  (checklist) |  | √ | √ | √ | √ | √ | √ |  | Descriptive statistics |
|  | Intervention Fidelity  (checklist) |  | √ | √ | √ | √ | √ | √ |  | Descriptive statistics |
| 2 | Satisfaction  (Client Satisfaction Questionnaire + 3 open ended questions) |  |  |  |  |  |  |  | √ | Descriptive statistics;  Content analysis |
| 3 | Lower extremity muscle strength (Time to perform one sit to stand) | √ |  |  |  | √ |  |  | √ | Means and SDs,  repeated measures ANOVA |
|  | Mobility  (2-minute walk test) | √ |  |  |  | √ |  |  | √ | Means and SDs, repeated measures ANOVA |
|  | Functional Status  (Barthel Index) | √ |  |  |  | √ |  |  | √ | Means and SDs,  repeated measures ANOVA |
|  | Quality of Life  (scale) | √ |  |  |  | √ |  |  | √ | Means and SDs,  repeated measures ANOVA |
| 4 | Discharge Destination  (Chart review) |  |  |  |  |  |  |  | √  (At the time of discharge from the TCU or within 60 days of admission to TCU, whichever comes first) | Descriptive statistics |

T1=time 1; T2=time 2; T3=time 3; ANOVA=analysis of variance; SDs=standard deviations.

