**Primary Outcome**

**Feasibility.** will be measured through recruitment rate, retention rate, and adherence (41).

**1. Recruitment rate.** Recruitment rate will be calculated as the percentage of participants who enroll in the study out of the total number of eligible participants (23). Reasons for nonenrolment and ineligibility for the study will also be recorded. A recruitment rate of >50% is considered moderate (40).

**2. Retention rate.**  Retention rate will be calculated as the percentage of participants who complete the study (i.e., receive the full dose of the intervention and provided post-test outcome data) out of the number of participants who were enrolled (i.e., signed a consent form and provided baseline data) (41). A retention rate of ≥80% is considered high (40).

**3. Adherence.** Participants’ adherence will be determined by: 1) the number of treatment sessions attended; and 2) the level of engagement with the treatment (41). For this study, the planned number of sessions is five per week for 6 weeks for a total of 30 sessions. Thus, client adherence will be measured in two ways: 1) as a percentage: the number of sessions attended divided by the total number of sessions (30 sessions); and 2) a) the duration of each walking session, duration of each intervention session, and number of sit to stands done per session; and 2) b) the number of sit to stands done per session, divided by the goal number of sit to stands (see Table 1). Participant’s adherence to treatment will be documented by the interventionist using an adherence checklist created for this study (Appendix S) immediately after each intervention session. An adherence of ≥75% is considered high (28).

**Intervention fidelity.** Intervention fidelity will also be measured through the interventionist’s self-report of 12 intervention items (41). The percentage will be calculated as the number of items done divided by the 12 items on the intervention fidelity checklist. Immediately after each session, the interventionist will document the specific activities provided during the session using a structured checklist (Appendix S) created for this study, which includes the specific activities that were done during each session. Any safety events (such as falls) that occur during the intervention sessions will also be documented.

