# STATISTICS

**Sample Size**

An activity-based study involving older adults with dementia in the nursing home setting (31) that used time to perform one sit to stand found a moderate effect size (Cohen’s d) of 0.48. Since the present study will use repeated measures ANOVA, a Cohen’s *f* of 0.25 (a suggested value for moderate effect size) (55) was used in the sample size calculation. Based on an *f* of 0.25, a power of 0.8 and an alpha of 0.1, in keeping with those used in a mobility study involving older adults with dementia (23), a sample of 21 participants will be needed for this study. Using an alpha of 0.1 can be acceptable for exploratory or preliminary studies (56) (p. 188). An attrition rate of just under 20% over the course of a 6-week study will be taken into account, as was experienced in a 6-week intervention study involving older adult residents with dementia (28). Thus, a sample of 26 participants will be recruited for this study. G*Power 3.1.9.7 software (57) was used for the sample size calculation for an ANOVA: Repeated measures, within factors statistical test with one group, three measurements, 0.6 for the correlation among repeated measures, and 0.8 for nonsphericity correction (which is a mild departure from sphericity) (56).

The sample size is achievable based on input provided by our collaborating TCP administrators, as the TCP has a 35-bed capacity and most patients have cognitive impairment.

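### Discharge before the end of week 6 ends data collection with no exit assessment and is counted like a refusal, so the T1–T3 change depends on staying in the unit and the retention figure mixes discharge with withdrawal

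*Protocol*

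**What the plan says.** Four parts of the Protocol act together.

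- **Stopping rules or discontinuation criteria:** "Once they are discharged (including back to acute care, another site or back home) we will discontinue collecting data on the patient". What remains after that point is the destination: "we will keep track of their discharge disposition".
- **Table 2:** strength, the two-minute walk test, the Barthel Index and quality of life are measured at T1, at week 4 (T2) and at "Posttest (Immediately after 6-week intervention) (T3"). No outcome assessment at discharge is listed.
- **Primary Outcome, Retention rate:** the numerator is those who "receive the full dose of the intervention and provided post-test outcome data", taken "out of the number of participants who were enrolled (i.e., signed a consent form and provided baseline data"). The target is at least 80%. Reasons for not enrolling are to be recorded, but no breakdown of reasons for not being retained is called for.
- **Sample Size:** 21 participants are needed and 26 are recruited. The attrition allowance of just under 20% is set "as was experienced in a 6-week intervention study involving older adult residents with dementia". No separate allowance is made for discharge, and Plan for Missing Data does not name discharge as a cause of missing outcomes.

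Baseline timing also matters. Under Data Collection, "outcome data at T1 will be obtained within the first month of" admission to the unit.

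**The concern.** Leaving the unit is an expected event here. The Literature review describes these programmes as short-term, research question 4 asks what share of participants go home, and no eligibility criterion requires an expected stay of six weeks or more.

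Two results are affected.

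1. **T1–T3 change.** It can be computed only for participants still in the unit at the end of week 6. Remaining there plausibly depends on the function being measured: some leave because they have improved, others because they return to acute care. The comparison is therefore conditional on an event related to the outcome.
2. **Retention, a primary feasibility outcome.** One percentage combines people who declined to continue with people who were discharged. These carry different messages for a later trial. The first concerns the intervention, and the second concerns whether a six-week programme fits the stay.

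A later analysis plan cannot repair the first problem, because it cannot analyse measurements that the protocol says not to take.

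**Working it through.** **Step 1: reproduce the plan's sample size.** Inputs from Sample Size: f = 0.25, alpha = 0.10, power 0.80, m = 3 measurements, correlation ρ = 0.6, nonsphericity ε = 0.8, one group. For the within-factors repeated-measures ANOVA:

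- λ = f² × N × m × ε / (1 − ρ)
- df1 = (m − 1)ε
- df2 = (N − 1)(m − 1)ε

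At N = 21, λ = 0.0625 × 21 × 3 × 0.8 / 0.4 = 7.875, df1 = 1.6 and df2 = 32, which gives power 0.811. At N = 20 the power is 0.792. So 21 is reproduced. With 19% attrition, 21 / 0.81 = 25.9, which rounds up to 26. That is reproduced too.

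**Step 2: the margin.** 26 − 21 = 5 losses, and 5/26 = 19.2%. The retention criterion has the same limit:

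- 21/26 = 80.8%, meets 80%
- 20/26 = 76.9%, does not

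Both the power target and the retention target therefore allow five losses of any kind.

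**Step 3: what happens to a participant discharged before the end of week 6.**

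| Quantity | Source | Result |
|---|---|---|
| T3 outcomes | Stopping rules; Table 2 | none |
| Retention numerator | Primary Outcome | not counted |
| Retention denominator | Primary Outcome | counted |
| T1–T2 change | Table 2; Plan for Analysis (paired t-tests if data are missing) | available if discharged after the week-4 assessment |
| T1–T3 change | same | not available; the paired test also needs T3 |
| Discharge destination | Stopping rules; Table 2 | recorded |

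**Step 4: how long a participant must stay.** T1 falls between admission and about day 30. If the intervention starts straight after T1, T3 falls between day 0 + 42 = 42 and day 30 + 42 = 72 of the stay.

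**Step 5: sensitivity to the discharge rate.** The Protocol gives no probability q of discharge between T1 and T3, so q is an assumed range. With independent losses, expected retention is (1 − d)(1 − q), where d is other attrition. The chance of retaining at least 21 of 26 is a binomial tail.

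| Assumed q | Chance of meeting 80%, d = 0 | Chance of meeting 80%, d = 19% |
|---|---|---|
| 0% | 1.00 | 0.63 |
| 10% | 0.96 | 0.25 |
| 20% | 0.58 | 0.06 |
| 30% | 0.16 | 0.01 |
| 40% | 0.02 | 0.001 |

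ANOVA power is 0.79 with 20 completers, 0.75 with 18 and 0.70 with 16.

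**Step 6: what separating the losses would show.** Suppose 20 complete and 6 are lost.

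- All six discharged: 20/26 = 76.9% of all enrolled; 20/(26 − 6) = 100% with discharges taken out of the denominator.
- All six refused: 20/26 = 76.9% on both measures.

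The planned single figure cannot distinguish these two situations.

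**The case against.** The strongest reply is that counting discharge as non-completion is a legitimate choice. Whether six weeks of sessions fit within a TCU stay is something a feasibility study ought to learn, and acceptability has its own measures in attendance, engagement and satisfaction. This stands, and it is why the all-enrolled rate should be kept. It does not explain why that rate should be the only one, or why no outcome is measured at a planned exit.

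It can also be said that destination is tracked and withdrawal is described separately, so the split could be produced afterwards. That is true for the retention breakdown, although none is planned. It does not help the missing outcome measurements.

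Four stronger readings are tempting, and the documents do not support them.

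- **That the retention rate describes only those who stayed.** Its denominator is everyone enrolled with baseline data; only the numerator is limited to stayers.
- **That early leavers contribute nothing to efficacy.** Those discharged after week 4 have T2 values, and the paired-test fallback can use them for T1–T2.
- **That T3 is lost whenever it falls after day 60.** The 60 days in Table 2 are a cut-off for recording discharge destination. They are not a maximum stay, and the wording allows longer stays.
- **That the efficacy result is biased in a known direction, or that retention will probably fail.** No length of stay or discharge rate is given. Departures home and returns to acute care could pull in opposite directions. The Setting section says the Abbeylawn patients are destined for long-term care, and the Literature review says many programme patients are waiting for a nursing home. Stays may therefore be long for some, and the problem correspondingly smaller.

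**Conclusion.** The point holds as a gap in the protocol's data collection and reporting. As written, discharge before the end of week 6, to any destination, leaves no T3 outcome and is scored as non-retention. The T1–T3 change is therefore conditional on remaining in the unit, with bias of unknown sign and size. The retention figure mixes two kinds of loss within a margin of five, and a sixth loss of either kind takes it from 80.8% to 76.9%.

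The 21/26 and 20/26 results are arithmetic on the plan's own numbers. The probabilities of meeting the criterion rest on an assumed discharge rate and independent losses, and show sensitivity only. That leaving the unit is related to function is plausible, but the documents do not demonstrate it. The change is worth making before enrolment because it is cheap and the missing measurements cannot be recovered later.

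**What to change.** **Stopping rules and Table 2.** Add the same T3 tests shortly before a planned TCU discharge that falls before the end of week 6, and record the number of weeks of intervention received.

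**Plan for Analysis.** Keep the fixed week-6 T3 analysis as planned. Add a sensitivity analysis that uses the exit measurement for participants discharged early.

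**Primary Outcome, Retention rate.** Keep the all-enrolled completion rate and judge it against 80%. An exit measurement would not turn an early leaver into a retained participant, since the definition also requires the full dose. Beside that rate, report:

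- the number lost to TCU discharge, by destination;
- the number lost to withdrawal or refusal;
- the retention rate with TCU discharges removed from the denominator.

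**Cost.** Protocol wording, and the existing T3 session (45 minutes by the Protocol's own estimate) brought forward for planned early discharges. Planned destination is already to be obtained from the chart or unit staff, so asking for the planned date adds little. Two limits remain: exposure at the exit measurement will vary, which is why it belongs in a sensitivity analysis, and unplanned transfers to acute care will still be missed.

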## Setting

Transitional Care Unit (TCU) in Abbeylawn Retirement home in Pickering, Ontario and TCU in Cedarbrook Lodge Retirement Home in Scarborough Ontario. The Abbeylawn TCU admits patients designated as ALC and are destined to go to long-term care and has a 35-bed capacity. From December 2023-May 2024 (or, for 6 months from the actual start date of the study), patients will be enrolled in the study on an ongoing basis. Up to 8 patients will be enrolled in the study at a given time.

# SELECTION OF PARTICIPANTS

##

## Inclusion criteria

Older adults will be eligible if they meet the following criteria: 1) aged 65 years and older;

2) have cognitive impairment (dementia, delirium, cognitive impairment, or unspecified cognitive impairment) as documented in the medical record or Quick Dementia Rating Scale (QDRS) score of ≥2) (Appendix A); 3) admitted to a transitional care unit after a hospitalization; 4) can speak English; 5) has received clearance from the physiotherapist to participate in the study; 6) has received clearance from the nurse practitioner to participate in the study; 7) were community-dwelling (lived in a home or retirement home; not a nursing home) prior to hospitalization; 8) Were able to walk independently or with the assistance of one person (with or without a gait aid) prior to hospital admission; 9) is currently able to ambulate either independently or with the assistance of one person (with or without a gait aid); 10) has a care partner (family member, friend) who is willing participate in an interview about the patient for the study.

**Exclusion criteria**

Patients will be excluded if they are: 1) Palliative (having <six months prognosis as defined by Hui and colleagues (37)) as documented in the medical chart; 2) have Parkinson’s disease as documented in the medical chart (due to impairments in muscle and motor function) (23).

## Withdrawal of subjects

The patient, their SDM, or the care partner may withdraw from the study at any time. If they decide to leave the study, they will be presented with two choices: 1) the information that was collected before their withdrawal from the study will still be used to help answer the research question; 2) all information collected before their withdrawal will be destroyed. No new information will be collected without consent.

# DESCRIPTION OF INTERVENTION

**Description of the OASIS Walking Intervention**

The Older Adults with cognitive impairment performing the Sit to Stands and Walking Intervention is a nurse-led intervention that consists of three components: 1) Patient-Centered Communication Care Plan (informed by interviews with the participant and their care partner); 2) Sit to Stand Activity; and 3) Walking program (Figure 4). This intervention is grounded using a patient centered approach. An intervention manual has been created for this study (Appendix B).

Prior to the in-person sessions involving sit to stand activity and walking, the interventionist will review the participant’s medical chart and will conduct interviews with the participant and their care partner. The care partner can be their SDM, a family member, or friend, as determined by the patient or SDM. These interviews will inform the content of the patient-centered communication care plan.

**Intervention Dose.** The dose of the intervention is: up to 45 minutes per session, five sessions per week, for six weeks. Approximately up to 30 minutes will be spent walking with the participant and up to 15 minutes will be spent performing the sit-to-stand activity. Hospitalized older adults may have some difficulty reaching a moderate intensity of dose at the onset of the study. Indeed, a gradual increase in walking distance, speed, and frequency of walking sessions was used in a similar study with good effect (35). As such, for the first two weeks, intensity and frequency of dose will be gradually increased as tolerated by the participant, until the goal dose of 30 minutes, 5 days a week is reached.

**Intervention Components**

**Component 1:** Patient-Centered Communication Care Plan. An individualized, patient-centered communication care plan will be created for each participant, which will be used to promote enjoyment and engagement during the in-person walking and sit to stand activity sessions. The care plan will be informed by interviews that the interventionist will have with the participant and their care partner. The interview with the care partner will be 45 minutes long and can be done in-person or over the phone, according to the preference of the care partner. Specific questions that the interventionist will ask the care partners (Appendix C) and participants (Appendix D) have been adapted from a question guide used in a study with residents with dementia in nursing homes (35, 50). The interventionist will also ask the care partner about the participants’ physical function prior to hospitalization (Barthel Index).

The interview with the participant will be 45 minutes in duration (30 minutes for interview; 15 minutes for communication tests) and done in person in the patient’s room, lounge, or preferred seated area at the TCU as per patient preference. The participant’s care partner may be present with the participant during the participant’s interview as per the participant’s preference and care partner’s availability. During the interviews, the interventionist will ask questions about three areas of a patient-centered assessment: 1) Participant’s biography (work history, family, interests); 2) Participant’s communication abilities and preferences; 3) Engagement with the Participant (35, 58) (Appendix R).

The information gained from the interviews will be added to the patient-centered communication template (Figure 5). The individualized care plan will be used during the walking and sit to stand activity sessions to promote enjoyment (e.g., talking about participant’s interests, family and friends), engagement (e.g., talking about things that help to motivate participant to continue walking), and communication (e.g., using glasses to help with walking).

**Component 2:** Sit to Stand Activity. The procedure for the sit to stand activity, which is adapted from the sit to stand protocol used by Barreca 2004 and colleagues (44), is outlined in Table A, which is embedded in the intervention manual (Appendix B).

Target Number of Sit to Stands. The interventionist or RA will measure the number of sit to stands that a participant can do in 30 seconds at baseline. The procedure for this test is outlined in Appendix B and is adapted from the procedure used in previous study (84). Based on that number, a target number of sit to stands to do per session will be determined, based on the algorithm used in the study by Slaughter and colleagues (48). Halfway into the intervention (after 3 weeks), the target number of sit to stands will be progressed. The target number of sit to stands and the algorithm used by Slaughter et al. (48) (Personal communication with [name] January 2023) is outlined in the following formula:

Target number of sit to stands per occasion = (Number of sit to stands done in 30 seconds at baseline +1)

Number of occasions per day = 2 occasions on day shift + 2 occasions on evening shift = 4

Target number of sit to stands per day = 4 x (Number of sit to stands done in 30 seconds at baseline +1)

In the Slaughter et al. study, the adherence to the sit to stand activity was much lower than what was targeted; the average enactment was two sit to stands per day (rather than the target of four) and three sit to stands per occasion (rather than the target of five), for an average of six sit to stands done per day per participant (48).

For this study, the interventionist will meet with participants for one session per day, 5 days per week. Based on the above algorithm and taking into consideration the actual enactment (48), the target number of sit to stands per session for the present study was calculated. The final target number (as calculated by Slaughter and colleagues) will be the same as the progressed target number for the second half of this intervention study (for weeks 4-6); the final target number (as calculated by Slaughter and colleagues) will be multiplied by ½ to form the target for weeks 1-3 of the present study. The algorithm for the present study is outlined in the following formula:

